### Cost-effectiveness analysis

Two health economic analyses will be conducted. The main analyses will be performed from the perspective of the NHS and personal social services, with secondary analyses from a societal perspective.

A within-trial analysis will compare GCS to no thromboprophylaxis over the 90 days of the study. Resource use items associated with treatments in hospital and community care will be collected using case notes and self-completed patient resource use diaries over the 90-day follow-up, and costed using manufacturers’ list prices, previous literature and national reference costs. Days off work and normal activities and other patient-related costs will be collected for a secondary analysis. EQ-5D will be collected at baseline and follow-up, analysed using the NICE approved tariff. Appropriate methods will be used to handle missing data and any relevant subgroups in line with the Statistical analysis plan.

If there are clinically relevant and measurable differences in VTE or QoL between the study arms at 90 days, a Markov (state-transition) decision model will be constructed to compare the Incremental Cost-Effectiveness Ratio (ICER) up to 2 years for GCS versus no GCS. The time horizon of the model will be 2 years allowing extrapolation of sequela of VTE events (such as post-thrombotic syndrome (PTS)) over the longer term to quantify the impact of VTE on patient health (quality adjusted life years (QALYs)) and resource use. A preliminary model has been constructed based on published literature to identify the key variables that would need to be collected during the clinical study, and to estimate the number needed to treat (NNT) to avoid one VTE, above which GCS would not be considered cost-effective at NICE thresholds. The 2-year time point was chosen as we know from previous research that the incidence of PTS after acute DVT levels out after the first year.

This preliminary model conservatively assumes 30% of patients with VTE develop PTS, with 3% of those patients having severe PTS. The cost of purchasing and applying GCS stockings is approximately £22.46.^19^ The model assumes the cost of treatment of VTE, non-severe and severe PTS, are £451, £872 and £1547, respectively, and estimates of the utility decrement associated with symptomatic VTE and PTS which are 0.8628, 0.7745 and 0.6752, respectively.^20^ Using a 2-year time horizon, the ICER of GCS versus no prophylaxis would be £20 603 per QALY if the NNT were 200 participants. Hence, for GCS to be cost-effective at a NICE willingness to pay threshold, the NNT would need to be below 200.

The health economic analyses will be conducted and reported according to NICE reference case and Consolidated Health Economic Evaluation Reporting Standards (CHEERS) guidelines,^21 22^ including sensitivity analyses and probabilistic sensitivity analyses. The results will be presented as estimates of mean incremental costs, effects and incremental cost per QALY.

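### The long-term economic model is conditional on an undefined 90-day difference, and its 2-year horizon rests on when new PTS cases level off, not on how long existing cases last

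*Protocol article*

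**What the plan says.** All of this is in the protocol article's section on cost-effectiveness analysis.

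- One analysis is unconditional: "A within-trial analysis will compare GCS to no thromboprophylaxis over the 90 days of the study".
- The long-term model is conditional: "If there are clinically relevant and measurable differences in VTE or QoL between the study arms at 90 days, a Markov" model is to be constructed. The article does not say what size of difference counts as relevant or what makes it measurable.
- On the horizon: "The time horizon of the model will be 2 years allowing extrapolation of sequela of VTE events". The only reason given is that "the incidence of PTS after acute DVT levels out after the first year".
- A separate model already exists: "A preliminary model has been constructed based on published literature to identify the key variables". It "conservatively assumes 30% of patients with VTE develop PTS, with 3% of those patients having severe PTS". On the intervention: "The cost of purchasing and applying GCS stockings is approximately £22.46". At 2 years it gives £20,603 per QALY at an NNT of 200, from which the article concludes: "Hence, for GCS to be cost-effective at a NICE willingness to pay threshold, the NNT would need to be below 200".
- Sensitivity and probabilistic sensitivity analyses are promised. A longer horizon is not named among them.

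**The concern.** There are two separate weaknesses.

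The first is the horizon. A plateau in incidence tells us when cases stop accruing. It says nothing about how long a person with PTS goes on having lower utility and using care, and the article gives no PTS duration. A case arising late in year 1 is credited with little more than one year of burden. Participants are 18-59, so there are many later years in which a burden could continue.

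The second is the trigger. Whether the long-term model is built depends on the observed result, by a criterion not fixed in advance. A real but modest benefit that fails the criterion gets no extrapolation. Estimates that pass it tend to be too large.

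The cut-off also sits where it matters. The design rates of 1.0% and 0.5% (sample size section) give an NNT of 1/0.005 = 200, the same number as the stated limit. If the true limit is higher, differences smaller than the powered one could still be good value.

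**Working it through.** **Inputs from the article.** Stockings £22.46 per patient. PTS after 30% of VTEs, 3% of those severe. Costs: VTE £451, non-severe PTS £872, severe PTS £1,547. Utility figures 0.8628, 0.7745 and 0.6752. These are labelled decrements, but read that way the ICER at NNT 200 is about £1,700-£8,400, far from the stated figure, so I treat them as utilities.

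**Assumptions the article does not give.** Comparator utility 1; VTE loss lasting 0.25 year; discounting at 3.5%; PTS cost either annual or one-off; threshold £20,000 to £20,603.

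**Formulas, per VTE averted**
- D = discounted years lived with PTS, per PTS case
- VTE loss = (1 − 0.8628) × 0.25 = 0.0343 QALY
- PTS loss per year = 0.3 × [0.97 × 0.2255 + 0.03 × 0.3248] = 0.3 × 0.2285 = 0.0685 QALY
- PTS cost = 0.3 × [0.97 × 872 + 0.03 × 1,547] = 0.3 × £892.25 = £267.68
- QALYs gained = 0.0343 + 0.0685 × D
- Cost saved = £451 + £267.68 × D (annual cost), or £718.68 (one-off cost)
- ICER = (NNT × 22.46 − cost saved) / QALYs gained
- Break-even NNT = (threshold × QALYs gained + cost saved) / 22.46

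**The article's own figure.** At 2 years D = 1 + 1/1.035 = 1.966, QALYs = 0.1691, and the annual-cost saving is £977. ICER at NNT 200 = (4,492 − 977)/0.1691 = £20,789, against £20,603 stated. Without discounting it is £20,455. Several other sets of assumptions also come within 1%, so this is a near match and not a unique reproduction.

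**Changing only the horizon and persistence.** Persistence is the yearly proportion of PTS cases continuing after year 2.

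| Horizon, persistence | D | QALYs | Break-even NNT, one-off cost | Break-even NNT, annual cost |
|---|---|---|---|---|
| 2 years | 1.966 | 0.169 | 183-187 | 194-199 |
| 5 years, 50% | 2.767 | 0.224 | 231-237 | 253-259 |
| 5 years, full | 4.673 | 0.355 | 348-357 | 392-401 |

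Within each range the lower value is at £20,000 and the upper at £20,603. Example, 5 years, full persistence, annual cost, £20,000: (20,000 × 0.3546 + 451 + 267.68 × 4.673)/22.46 = 392. If nothing remains after year 2, the first row applies at every horizon.

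**Check that does not need the 2-year state durations.** The stated ICER implies (4,492 − 719)/20,603 = 0.183 QALY (one-off cost) or (4,492 − 986)/20,603 = 0.170 QALY (PTS cost in each of 2 undiscounted years). Adding only the years after year 2, at £20,000, with 50-100% persistence and comparator utility 0.86-1.0, gives a 5-year break-even of about 215-393. The direction is the same throughout.

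**Effect of the unstated threshold.** With the same implied QALYs, the 2-year break-even is about 195 at £20,000. At £30,000 it is (30,000 × 0.170 + 986)/22.46 = 271 to (30,000 × 0.183 + 719)/22.46 = 277.

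**The trigger.** This is a matter of reading, not arithmetic. The figure of 200 comes from the literature model already built, so the trigger cannot move it. The trigger governs only whether the trial's own result is extrapolated.

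**The case against.** The strongest reply has four parts.

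- The documents give no PTS duration beyond 2 years, so they do not show that 200 is too low. This stands. A reader might infer that the limit is simply wrong, or two to three times too small. That needs full persistence for 5 to 10 years, which the article neither states nor excludes.
- A reader might also infer a reversed verdict at the edge of significance. With 21,472 × 0.85/2 = 9,126 per arm, 365 per site and design effect 1 + [(1 + 0.25²) × 365 − 1] × 0.001 = 1.387, the standard error is √[1.387 × (0.01 × 0.99 + 0.005 × 0.995)/9,126], or 0.150 percentage points. A difference of 0.295 points (NNT 339) would then be significant, poor value at 2 years and good value at 5. This holds only with comparator utility 1 and full persistence. At 80% persistence the 5-year break-even is 298-331, and at comparator utility 0.9 with full persistence it is 206-250, both below 339. Nor does the article equate its trigger with significance.
- The 90-day analysis runs regardless, a quality-of-life difference alone can trigger the model, and with truly no difference there is nothing to extrapolate. All true. But an imprecise result is not evidence of no difference, and 90 days ends before the point at which the article says new PTS cases level out.
- Probabilistic analysis is already planned, the £20,603 is already stated for 2 years, and horizon scenarios are often left to a fuller plan. This stands as far as it goes. The point rests on the reason the article does give, which does not support the horizon.

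**Conclusion.** The point holds in a limited form. The reason given for 2 years does not address how long PTS lasts, and the long-term model depends on an undefined observed difference. Any burden persisting past year 2 raises the break-even NNT above its 2-year value. The direction is firm. The size depends on PTS duration, comparator utility, cost recurrence and threshold, none of which is stated. The trigger's net bias has no fixed direction: it can omit a true modest benefit, or extrapolate mainly from estimates that are too large. A reader might conclude that trigger and horizon together distort the whole economic answer; the documents do not support that. The primary outcome, sample size and main inference are untouched. This is a cheap improvement to a secondary analysis.

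**What to change.** - Run the Markov model whatever the 90-day difference, carrying the full uncertainty of the adjusted absolute risk difference into the probabilistic analysis already planned.
- Keep 2 years as the base case if wished, but justify it by PTS duration, and prespecify longer-horizon scenarios with varied PTS persistence, including none. A lifetime base case is debatable and not needed to meet the point.
- Restate the NNT cut-off as conditional on the 2-year horizon and on a threshold given in pounds.

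The cost is a little modelling work, since a preliminary model exists, and the need to state persistence assumptions openly. No additional trial data are needed.

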### Data monitoring, safety and quality control

An independent TSC and independent Data Monitoring Committee (iDMC) have been appointed. The main role of the TSC will be to provide overall supervision of the trial and ensure that it is being conducted in accordance with the principles of Good Clinical Practice and the relevant regulations. The main role of the iDMC will be to safeguard the interests of trial participants and to monitor the main outcome measures including safety and efficacy. The clinical trial manager, together with the Trial Management Group, will oversee trial progress.

All treatment-related AEs (related to the GCS only) will be collected centrally at 7 days postprocedure, as will all serious adverse events (SAEs). The Chief Investigator (CI) will be notified of all SAEs within 24 hours. All SAEs will be reported to the Research Ethics Committee (REC) and sponsor if, in the opinion of the CI, the event was related to the intervention. These analyses will be descriptive, with any p values calculated to be interpreted descriptively.

### Patient and public involvement

During the grant application stage, online surveys were launched to learn public views on the PETS study. These surveys helped to inform important aspects of the trial, including the number of visits and questionnaires used in the study. Two patient advisors, both with lived experience of VTE, have been involved in the design of the study and review of patient-facing materials. Both were grant coapplicants, have agreed to sit on the TSC, facilitate patient advisory groups, will assist with the dissemination of results and are coauthors of this manuscript.

### Ethics and dissemination

Ethical approval was granted by the Camden and Kings Cross Research Ethics Committee (22/LO/0390). Amendments to the protocol will be updated on the ISRCTN record. All amendments to the protocol will be submitted to the sponsor for review before applying for approval from the REC and the Health Research Authority (HRA). Protocol amendments will be circulated by email to investigators and study nurses. Standard informed consent will be obtained by research nurses and investigators, with freedom to withdraw at any time. The findings from this study will be published in peer-reviewed journals, presented at national and international conferences and disseminated to participants (via emails and letters at the end of the study).
